## **METHODS**

This is a pilot, open label study in which the population will be formed by adult patients either gender, with CKD in pre-dialysis stage in Buenos Aires, Argentina, that fulfill the inclusion and exclusion criteria previously established.

Once signed the informed consent, the patients will be included in the study an initial check-up will be performed in order to evaluate clinical status and to assess haematology parameters in every patient.

After that the patients will receive intravenous Ferric Carboxymaltose (Ferinject ®) by the following therapeutic schedule:

Visit 2: IV FERINJECT ® 1000 mg in an infusion over 15-20 minutes.

Then, a monthly evaluation will be performed by six months.

During the time of the investigation there will be strict control of adverse effects in every patient and that will be recorded in the corresponding CRF.

### **Follow-up Phase:**

In each check-up, measurements of the haematological parameters will be taken so to assess the efficacy tolerability and potential adverse effect of Ferric Carboxymaltose (Ferinject ®) in every studied patient.

### **Chronogram of visits**

Initial Assessment (visit 1): It will be performed the day the patient enters the study once he/she has read and signed the Informed Consent regarding the participation in the study. In this assessment the following information will be collected:

- a) Demographic and anthropometric data: City and country of residence, age, sex, weight, height, occupation, socioeconomic strata.
- b) Medical History: Diagnosis associated.
- c) Physical Examination (Vital signs: blood pressure, heart rate, breath rate, etc).
- d) Blood samples for Hb, Hct. RBC, serum ferritin, transferrin saturation, creatinine clearance, and proteinuria.

[figure not shown]

[name]; PhD; FASN.  
 Professor of Medicine University of Buenos Aires  
 Chief of Nephrology.  
 Hospital Alemán, [name]  
 Buenos Aires (1118)- Argentina  
 [contact]  
 [contact]  
 Mobile [contact]  
 E-mail: [contact]

### Visit 2:

- a) Anamnesis and Physical Examination (Vital signs: blood pressure, heart rate, breath rate, etc).
- b) IV Ferinject ® 1000 mg administration.
- c) Evaluation of tolerability and adverse effects.

### Visit 3

- a) Anamnesis and Physical Examination (Vital signs: blood pressure, heart rate, breath rate, etc).
- b) Evaluation of tolerability and adverse effects.
- c) Blood samples for Hb, Htc. RBC, serum ferritin, transferrin saturation, creatinine clearance and proteinuria.

### Visit 4 to 8

- a) Anamnesis and Physical Examination (Vital signs: blood pressure, heart rate, breath rate, etc).
- b) Evaluation of tolerability and adverse effects.
- c) Blood samples for Hb, Htc. RBC, serum ferritin, transferrin saturation, creatinine clearance and proteinuria.
- d) Adjustment of medication according to the Hb and TSAT outcomes.

### Potential results post FERINJECT ®

### Measure to follow

|                                  |                                  |
|----------------------------------|----------------------------------|
| 1- Hb 12-13 (g/dl) TSAT (%) > 20 | NO Ferinject NO Epo              |
| 2- Hb 12-13 (g/dl) TSAT (%) < 20 | Ferinject 100mg NO Epo           |
| 3- Hb 11-12 (g/dl) TSAT (%) > 20 | NO Ferinject increase Epo 25%    |
| 4- Hb 11-12 (g/dl) TSAT (%) < 20 | Ferinject 200mg NO Epo           |
| 5- Hb 10-11 (g/dl) TSAT (%) > 20 | NO Ferinject increase Epo 25%    |
| 6- Hb 10-11 (g/dl) TSAT (%) < 20 | Ferinject 300mg increase Epo 25% |

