## **OBJECTIVE**

### *Primary:*

- To determine possible reduction in ESA requirements after intravenous 1g Ferric Carboxymaltose (FERINJECT ®) administration in patients with CKD in pre-dialysis stage, who were under a monthly EPO treatment and continuous oral iron therapy during the previous six months, in order to maintain a Hb value according to international recommendations.

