### **Inclusion Criteria**

- Patients over 18 years with chronic kidney disease (Creatinine Clearance  $\leq$  40 ml / min), and Hb between 11-12 g / dl, serum ferritin <100 mg / dl, or TSAT <20, being treated with a regular (monthly) institution schedule for EPO together with oral iron during the last 6 months before inclusion.

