## **STUDY DESIGN**

- Prospective study to 6 months with a single branch of patients who are treated with monthly EPO therapy together with oral iron for at least the last six months before the study and met inclusion criteria.
- From CKD database are randomly selected 30 patients. After signing an informed consent form in duplicate and with witness, duly authorized by the Committee on Education and Research institutions, all patients will receive intravenous 1g Ferric Carboxymaltose (FERINJECT ®) in one dose of 1000 mg on the recommendation of the product.
- On a monthly basis after intravenous 1g Ferric Carboxymaltose (FERINJECT ®) the administration, all patients will be controlled dosage of Hb by HemoCue, in order to dispense the EPO to maintain a baseline Hb level.
- Monthly checks will be carried to register: vital signs and weight control, and record of adverse reactions linked to 1g Ferric Carboxymaltose (FERINJECT ®) administration, registration HemoCue results.
- Before FERINJECT treatment and then every two months, all patients underwent blood control that includes: complete blood count haematimetric indexes, platelet count, serum iron, serum ferritin, TSAT, CRP, urea, creatinine, liver function tests).
- There will be collection of 24-hour urine to measure Creatinine Clearance and proteinuria at baseline and at the end of the study.

[figure not shown]

[name]; PhD; FASN.  
Professor of Medicine University of Buenos Aires  
Chief of Nephrology.  
Hospital Alemán, [name]  
Buenos Aires (1118)- Argentina  
[contact]  
[contact]  
Mobile [contact]  
E-mail: [contact]

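### At the entry haemoglobin, the post-dose EPO table contradicts the stated aim of holding baseline Hb, so the primary EPO change is partly set by the dosing rule

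*Protocol*

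**What the plan says.** The primary objective is "To determine possible reduction in ESA requirements after intravenous 1g Ferric Carboxymaltose". The Hb condition attached to that objective is worded "in order to maintain a Hb value according to international recommendations". The Study Design section describes a single arm with monthly Hb checks, "in order to dispense the EPO to maintain a baseline Hb level". The laboratory entry criteria are "Hb between 11-12 g / dl, serum ferritin <100 mg / dl, or TSAT <20". Patients must also have taken EPO and oral iron for the six months before entry, and the protocol describes that earlier regimen only as "being treated with a regular (monthly) institution schedule for EPO".

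The visit schedule lists medication adjustment by Hb and TSAT under Visits 4 to 8. The table under Potential results post FERINJECT / Measure to follow sets the action. For the entry Hb band with low TSAT, the table has "4- Hb 11-12 (g/dl) TSAT (%) < 20 | Ferinject 200mg NO Epo". For the same Hb band with higher TSAT, it has "3- Hb 11-12 (g/dl) TSAT (%) > 20 | NO Ferinject increase Epo 25" (per cent). Both rows for Hb 12-13 say no EPO, for example "1- Hb 12-13 (g/dl) TSAT (%) > 20 | NO Ferinject NO Epo". Both rows for Hb 10-11 raise EPO by 25%.

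**The concern.** The dose that the table dictates is also the primary outcome, so the rule must follow the stated aim. At the entry Hb it does not. A patient at baseline Hb is given either no EPO or 25% more, and no row is labelled as continuing the dose that kept Hb there.

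The direction makes this worse. Raising TSAT from below to above 20 at an unchanged Hb is a result the infusion aims for, yet it switches the instruction from no EPO to an increase. A patient whose TSAT stays below 20 keeps the no-EPO instruction.

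With 30 patients and no control arm, a fall or rise in mean EPO could come from iron, from the table, or from both. A statistical analysis plan could not repair this, because the rule changes the doses actually given.

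**Working it through.** **1. The texts side by side, for a patient at Hb 11-12**

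| Source in the protocol | What happens to EPO |
|---|---|
| Primary objective | Dosed to an internationally recommended Hb; no value given |
| Study Design | Dispensed monthly to hold baseline Hb |
| Table row 4, TSAT below 20 | No EPO, plus iron |
| Table row 3, TSAT above 20 | Increase of 25%, no iron |

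**2. Two readings of the no-EPO instruction**

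- *None is dispensed.* An entrant with TSAT below 20 who does not respond stays in row 4 and is recorded as a reduction.
- *No increase.* Rows 1, 2 and 4 leave the dose alone, and rows 3, 5 and 6 raise it. No row lowers EPO, so the table cannot produce the reduction the trial seeks.

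Under either reading, a patient at baseline Hb with TSAT above 20 is escalated. Entry needs low ferritin or low TSAT, so this includes a patient who entered on ferritin with TSAT already above 20.

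**3. Gaps in the table**

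- Hb 11.0 and 12.0 each fall in two bands. Hb 12.0 with TSAT above 20 gives no EPO (row 1) and +25% (row 3), and 12.0 is an eligible entry value.
- Hb below 10, Hb above 13 and TSAT exactly 20 have no row.
- A 25% increase has no base dose after a stop.
- Study Design schedules TSAT every two months; the visit list takes it at each of Visits 3 to 8.
- The pre-study institutional schedule is not described.

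**4. Illustrative bounds**

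The protocol gives no effect size or power figure to reproduce. Assumptions: prior monthly dose = 1; six monthly doses; Hb stays at 11-12; EPO has no feedback on Hb. The timing of Visit 3 is not stated, so the first adjustment is placed at month 1 (five changed doses) or month 2 (four).

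Row 4 throughout:
- stop: 1/6 - 1 = -83%, or 2/6 - 1 = -67%
- no increase: 0%

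Row 3 throughout:
- from month 1: (1 + 1.25 + 1.5625 + 1.953 + 2.441 + 3.052)/6 = 11.26/6 = 1.876, or +88%; the last dose is 1.25^5 = 3.05 times baseline
- from month 2: (1 + 1 + 1.25 + 1.5625 + 1.953 + 2.441)/6 = 9.21/6 = 1.535, or +53%
- table applied only at two-monthly TSAT checks, two steps: (1 + 1 + 1.25 + 1.25 + 1.5625 + 1.5625)/6 = 1.271, or +27%
- the same, three steps: (1 + 1.25 + 1.25 + 1.5625 + 1.5625 + 1.953)/6 = 1.430, or +43%

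75% of patients in row 4 and 25% in row 3:
- stop, month 1: 0.75 × (-0.833) + 0.25 × 0.876 = -0.41
- stop, month 2: 0.75 × (-0.667) + 0.25 × 0.535 = -0.37
- no increase: 0.25 × 0.876 = +0.22, or 0.25 × 0.535 = +0.13

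The sign of the mean change therefore depends on a term the protocol does not define.

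**The case against.** A reader might infer that the table alone fixes the endpoint whatever iron does, and that any unchanged patient is taken off EPO. The protocol does not support either inference.

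- The rows are indexed by Hb and TSAT, which iron is meant to move. A real rise to Hb 12-13 leads to no EPO, and a fall to 10-11 leads to an increase. The table is a feedback rule that distorts the outcome without wholly determining it.
- An unchanged patient loses EPO only if TSAT is below 20 and the instruction means a stop. An unchanged ferritin entrant with TSAT above 20 is escalated.
- The bounds switch the feedback off. They hold Hb at 11-12 while EPO is zero or compounds to three times baseline. Row 4 also gives 200 mg of iron each time, so five applications would add 5 × 200 = 1000 mg. It is not a test of one inert infusion.
- It is tempting to say the comparison also sets two different dosing rules against each other. The pre-study schedule is not described, so a difference is possible but not shown.
- This is a small, open-label pilot.

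These points limit how far the figures can be pressed. They do not remove the conflict between the table and the Study Design section at the entry Hb, and neither reading of the no-EPO instruction resolves it.

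**Conclusion.** The concern holds in a limited form. At the entry Hb of 11-12 the table conflicts with dispensing EPO to hold baseline Hb, a key instruction is undefined, and the bands overlap and leave gaps. The pre/post EPO change is therefore partly set by the algorithm, and a single-arm design cannot separate that part from an iron effect.

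The possible size is large, but it is known only as extremes under the fixed-Hb, no-feedback assumption and the timings shown. The true distortion lies somewhere inside those extremes and cannot be estimated from the protocol. The contradiction itself does not depend on those assumptions.

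**What to change.** Before first dosing, the sponsor should reconcile the primary objective, the inclusion criteria, the Study Design section, the visit schedule and the table. No clinical rule is proposed here. The amended text should:

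- state one Hb goal that governs EPO;
- assign every Hb/TSAT value to exactly one row;
- define the no-EPO instruction and the dose to which a 25% change applies, including after a stop;
- match the TSAT schedule to the visits at which the table is used;
- describe the pre-study dosing rule and say whether it differs from the table.

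In the analysis, report the pre/post Hb difference beside the EPO change and tabulate EPO changes by the row that triggered them. Do not attribute to iron any reduction made under row 4 without an Hb or TSAT response.

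An index of EPO per kg divided by Hb is optional and is no cure by itself. At constant Hb and weight it falls by the same 83% in the row 4 stop case.

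The cost is an amendment centred on one table, plus extra tabulation from data already collected. The apparent reduction may become smaller.

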## **VARIABLES**

### *1-Dependent Variables*

- Heart rate
- Breath rate
- Blood pressure
- Severity of the Anemia: According to the classification established by the WHO.
- Hemoglobin: substance inside erythrocytes consisting of a protein that binds iron
- Hematocrit: Proportion of erythrocytes in plasma
- Mean Corpuscular Volume (MCV): cellular index that reflects erythropoiesis.
- Serum Ferritin
- Percentage of transferrin saturation
- Creatinine Clearance
- Proteinuria
- Amount of Erythropoietin.
- Number of transfusions
- Number of hospitalizations
- Death
- Cause of Death
- Adverse Events: Appearance of adverse reactions in the organism with the treatment administered. Among others: nausea, vomiting, headache, diarrhea, allergy and hypotension.

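### At the entry Hb range the adjustment table lets TSAT decide whether EPO is stopped or raised, which conflicts with dosing to the baseline Hb and makes the primary quantity partly a product of the table

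*Protocol*

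**What the plan says.** - **Objective, Primary:** "To determine possible reduction in ESA requirements after intravenous 1g Ferric Carboxymaltose", in patients treated with monthly EPO and oral iron over the previous six months. Under Dependent Variables the quantity is listed only as "Amount of Erythropoietin".
- **Inclusion Criteria:** "Hb between 11-12 g / dl, serum ferritin <100 mg / dl, or TSAT <20". A patient can therefore enter on TSAT or on ferritin alone.
- **Study Design:** one arm followed for six months. Hb is checked monthly "in order to dispense the EPO to maintain a baseline Hb level".
- **Chronogram of visits, Visit 4 to 8:** "Adjustment of medication according to the Hb and TSAT outcomes". Visit 3 lists no such step.
- **Measure to follow, row 4:** "4- Hb 11-12 (g/dl) TSAT (%) < 20 | Ferinject 200mg NO Epo".
- **Measure to follow, row 3:** "3- Hb 11-12 (g/dl) TSAT (%) > 20 | NO Ferinject increase Epo 25" per cent.
- **Measure to follow, row 6:** "6- Hb 10-11 (g/dl) TSAT (%) < 20 | Ferinject 300mg increase Epo 25" per cent.
- **Measure to follow, rows 1 and 2 (Hb 12-13):** no EPO, whatever the TSAT.

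**The concern.** Row 4 describes the entry state of a patient admitted with TSAT below 20. If Hb and TSAT are still there at an adjustment visit, the table orders no EPO. A patient at the same Hb whose TSAT has been corrected is ordered 25% more. Under the Study Design rule, a patient already at baseline Hb gives no reason from Hb for either change.

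The amount of EPO is the primary quantity and no control arm is dosed by the same table. EPO withheld by order therefore cannot be told apart from EPO no longer needed. A reported reduction could come partly from patients whose iron deficit persisted, and a real iron effect at a steady Hb could be recorded as an increase. A statistical analysis plan could not repair this alone, because the dosing rule generates the data.

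**Working it through.** The protocol states no effect size, SD or power, so there is no figure of its own to reproduce. The check adds up EPO from the table's own orders.

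**Assumptions**
- The prior dose is D per month, so the six prior months total 6D. The comparison is six months after against six months before.
- Month 1 is at D, because Visit 3 lists no adjustment. Visits 4 to 8 then give five adjusted monthly doses.
- The no-EPO order means a dose of zero.
- The protocol does not say what the 25% is taken from. Two readings are shown: 25% of the baseline dose (each raised dose is 1.25D), and compounding on the last non-zero dose.

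**Same Hb throughout (11-12), TSAT the only difference**
- Row 4 at all five visits: D + 5 × 0 = 1.00D. Change = 1.00/6 - 1 = **-83%**.
- Row 3 at all five visits, of baseline: D + 5 × 1.25D = 7.25D. Change = 7.25/6 - 1 = **+21%**.
- Row 3 at all five visits, compounding: D(1 + 1.25 + 1.25² + 1.25³ + 1.25⁴ + 1.25⁵) = 11.26D. Change = **+88%**.

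**Hb falls after EPO is stopped, TSAT still low (rows 4 and 6 mixed)**

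With k visits in row 4 and 5 - k in row 6, the total is D[1 + 1.25(5 - k)] of baseline, or D[1 + 1.25 + … + 1.25^(5-k)] compounding.

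| Visits in row 4 | Of baseline | Compounding |
|---|---|---|
| 1 | 6.00D, 0% | 8.21D, +37% |
| 2 | 4.75D, -21% | 5.77D, -4% |
| 3 | 3.50D, -42% | 3.81D, -36% |
| 4 | 2.25D, -62.5% | 2.25D, -62.5% |
| 5 | 1.00D, -83% | 1.00D, -83% |

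A net reduction needs at least two of the five visits in row 4.

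**Group level**

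Let q be the share with TSAT below 20. Hold Hb at 11-12 and TSAT at its entry value, and take equal prior doses.
- One adjustment visit: mean change = -q + 0.25(1 - q) = 0.25 - 1.25q, which is zero at q = 0.20.
- Six months, of baseline: mean total = q(1.00D) + (1 - q)(7.25D) = (7.25 - 6.25q)D. This equals 6D at q = 0.20. At q = 0.50 it is 4.125D, or -31%.
- Six months, compounding: (11.26 - 10.26q)D. This equals 6D at q = 5.26/10.26 = 0.51. At q = 0.50 it is 6.13D, or about +2%.

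With half the patients below 20, an infusion with no effect thus reads as -31% or +2%, depending only on how the 25% is read. The documents do not give q.

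**The case against.** **The table as a whole follows response.** A reader might infer that iron failure always lowers recorded EPO and iron success always raises it. The table does not support that. Row 1 stops EPO after a full response (Hb 12-13, TSAT above 20), and row 6 raises it when Hb has fallen and TSAT is still low. The inverse direction holds only within Hb 11-12.

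**One visit is not the six-month result.** If a patient still needs EPO, stopping it should lower Hb and row 6 brings EPO back. One row-4 visit then nets 0% or +37%. The -83% case requires Hb to hold at 11-12 for five visits without EPO, and such a patient arguably does need less. Row 4 also gives a further 200 mg of Ferinject. All of this stands and limits the size. It does not remove the problem, because EPO is still assigned by TSAT at an unchanged Hb.

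**A non-responder need not be in row 4.** A patient admitted on ferritin with TSAT above 20, and unchanged, falls in row 3 and is raised. This stands, and it is why the group effect has no fixed sign.

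**The no-EPO order might mean no increase.** That would remove the row-4 reduction. It is the weaker reading: in the same column the matching Ferinject wording means not given, and no row would then ever lower EPO. It remains an assumption.

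**The two sections may be complementary.** The Study Design section does not say that Hb is the only criterion, and the visit schedule names both Hb and TSAT. That is fair. But a dose that is stopped or raised at baseline Hb is still not one dispensed to maintain baseline Hb.

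**Significance.** It is tempting to claim that an inert infusion would give a significant reduction. With 12 of 30 patients below 20 at a single visit, the mean is -25% and a paired t-test gives p = 0.036. The differences take only two values, however, and the signed-rank test gives p = 0.19. The documents do not support a claim of false significance.

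**Conclusion.** The point holds for Hb 11-12. Rows 3 and 4 conflict with the Study Design rule for a patient at baseline Hb, and in that band the primary quantity is partly set by TSAT, against the direction of iron correction. For one patient over six months the range runs from -83% (row 4 throughout) to +21% or +88% (row 3 throughout). A net reduction from rows 4 and 6 appears only from two row-4 visits onward (-21% or -4%).

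These figures assume that EPO is withheld under the no-EPO order, that month 1 is at the prior dose, and that there are five adjustments. The group result also depends on the unstated share with TSAT below 20 and can be wrong in either direction. It does not follow that every non-responder is counted as a success, or that the primary result must favour Ferinject.

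**What to change.** 1. Reconcile rows 3 and 4 of the adjustment table with the Study Design section so that one stated rule governs EPO. This review does not say which rule. State also what the no-EPO order means and what the 25% is taken from.
2. Record in the CRF the table row applied at each visit, and report EPO by row.
3. Add a supportive version of the primary comparison. In it, EPO changes at Hb 11-12 made because of TSAT, row-4 withholding and row-3 increases alike, are replaced by the last dose dispensed before the change. Changes under rows 1 and 2 stay as observed, since they occur above the entry range and may be true benefit. For the two fixed-Hb patients above, this gives D + 5D = 6D, or 0%, so neither direction is favoured. It cannot undo the effect of a withheld dose on later Hb, so it should not be a condition for success.
4. Attribute a reduced requirement to Ferinject only with this version shown beside the main result.

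The cost is a clarification of protocol wording, one CRF field and one extra table. The reported reduction may be smaller.

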### Visit 9 (end of the study):

- a) Final evaluation

[figure not shown]

[name]; PhD; FASN.  
Professor of Medicine University of Buenos Aires  
Chief of Nephrology.  
Hospital Alemán, [name]  
Buenos Aires (1118)- Argentina  
[contact]  
[contact]  
Mobile [contact]  
E-mail: [[contact]](mailto:[contact])

### **Patient withdrawal**

All patients of the population study may withdraw any time from the investigation by own will or by the investigator's decision before the occurrence of any adverse effect or transitory disease that could alter the results of the study or that represents a contraindication for the administration of the medicine. The reasons for withdrawal will have to be documented.

[figure not shown]

[name]; PhD; FASN.  
 Professor of Medicine University of Buenos Aires  
 Chief of Nephrology.  
 Hospital Alemán, [name]  
 Buenos Aires (1118)- Argentina  
 [contact]  
 [contact]  
 Mobile [contact]  
 E-mail: [contact]

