### *Secondary:*

- To assess the number of hospitalizations pre (six months) and post (six months) intravenous 1g Ferric Carboxymaltose (FERINJECT ®) administration in patients with CKD in pre-dialysis stage.
- To record the need for transfusion pre (six months) and post (six months) intravenous 1g Ferric Carboxymaltose (FERINJECT ®) administration in patients with CKD in pre-dialysis stage.
- To evaluate renal function as measured by Creatinine clearance and proteinuria of 24 hours, pre (six months) and post (six months) intravenous 1g Ferric Carboxymaltose (FERINJECT ®) administration in patients with CKD in pre-dialysis stage.
- To analyze the number of adverse reactions and complications due to intravenous 1g Ferric Carboxymaltose (FERINJECT ®) administration in patients with CKD in pre-dialysis stage.

[figure not shown]

[name]; PhD; FASN.  
Professor of Medicine University of Buenos Aires  
Chief of Nephrology.  
Hospital Alemán, [name]  
Buenos Aires (1118)- Argentina  
[contact]  
[contact]  
Mobile [contact]  
E-mail: [contact]

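### The investigator may withdraw a patient because an adverse effect or illness could change the study's results, and no follow-up is provided afterwards, so selection on outcome is possible

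*Protocol*

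**What the plan says.** The Patient withdrawal section lets a patient leave the investigation at any time, at the patient's own wish or by the investigator's "decision before the occurrence of any adverse effect or transitory disease that could alter the results of the study". A separate ground follows: "or that represents a contraindication for the administration of the medicine". One condition is attached: "The reasons for withdrawal will have to be documented". Taken literally, the investigator's decision would come ahead of the event. I read it as upon the event. Withdrawal in anticipation of an event would be no better.

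The design is described under STUDY DESIGN as "Prospective study to 6 months with a single branch of patients" and under METHODS in the words "This is a pilot, open label study". The primary objective is a reduction in ESA requirement. The secondary objectives compare hospitalisations, transfusion need and renal function in the six months before and after the infusion. A further one is "To analyze the number of adverse reactions and complications due to intravenous 1g Ferric Carboxymaltose". The list of dependent variables includes "Number of hospitalizations", the amount of erythropoietin, transfusions and adverse events.

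No section provides for visits or data collection after a patient has been withdrawn.

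**The concern.** The contraindication ground concerns the patient's safety. The other investigator ground concerns the study's results: an illness with no bearing on the safety of the medicine is enough if it might change what the study shows. The person who judges this knows the treatment and sees the outcomes as they accrue. The investigators carry out the follow-up themselves (Recruitment and training of the personnel), and information on effectiveness is taken every 4 weeks (ETHICAL ISSUES, item C).

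The events that permit withdrawal are tied to the outcomes. Adverse reactions are an outcome in themselves, and an intercurrent illness can lead to admission or transfusion. It can also reach the primary endpoint: EPO is dispensed against monthly haemoglobin, and the table of measures after the infusion includes EPO increases of 25% at Hb 10-11 g/dl. If such patients leave, those who remain have been selected partly on how they fared after dosing.

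At stake are the before-and-after comparisons of EPO, hospitalisation, transfusion and renal function. With one arm, nothing inside the study would show that the selection had happened.

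**Working it through.** The protocol states no effect size, standard deviation, event rate or withdrawal rate, so there is no figure of its own to reproduce. The check has two parts.

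**1. What is lost on withdrawal.**

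- The infusion of 1000 mg is given at Visit 2, and monthly evaluation follows for six months. Leaving after Visit 2 therefore costs mainly outcome data.
- Adverse effects are to be recorded in the CRF for every patient (METHODS), at Visit 2 itself (Chronogram of visits) and at every visit (DATA COLLECT METHODOLOGY, item 3). The event that prompts withdrawal should therefore be on file.
- What can be missing is everything later: EPO dose, admissions, transfusions and the end-of-study 24-hour urine collection. A statistical analysis plan can choose how to treat missing data, but it cannot recover data that were never collected.

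**2. How much selection could matter.**

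Inputs from the protocol: n = 30 (Study Sample); a t-test for Gaussian data and p < 0.05 (STATISTICS).

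Assumptions:
- each patient's standardised before-and-after change in EPO is normal with mean 0 and SD 1, positive being worse, so the true effect is zero;
- k patients are withdrawn and left out entirely;
- a paired, two-sided t-test is run on the remaining 30 − k, with t = mean / (SD / √(30 − k)) on 29 − k degrees of freedom.

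Withdrawal follows a score ρ·x + √(1 − ρ²)·e, where x is the patient's change and e is independent noise. The k highest scores leave. ρ = 1 removes the worst outcomes, ρ = 0.5 is partial dependence, and ρ = 0 is withdrawal unrelated to outcome. There were 40,000 runs per case.

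| k withdrawn | ρ | Bias in mean change (SD) | P(p < 0.05) | of which favouring the drug |
|---|---|---|---|---|
| 0 | – | 0.00 | 0.05 | 0.026 |
| 1 | 1 | −0.070 | 0.080 | 0.067 |
| 2 | 1 | −0.131 | 0.136 | 0.130 |
| 3 | 0 | 0.001 | 0.050 | 0.024 |
| 3 | 0.5 | −0.093 | 0.081 | 0.072 |
| 3 | 1 | −0.188 | 0.220 | 0.217 |
| 6 | 0 | 0.000 | 0.050 | 0.025 |
| 6 | 0.5 | −0.170 | 0.143 | 0.139 |
| 6 | 1 | −0.338 | 0.534 | 0.534 |

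Two checks on the table:
- Bias should scale with ρ. For k = 3, 0.5 × (−0.188) = −0.094, against −0.093 simulated. For k = 6, 0.5 × (−0.338) = −0.169, against −0.170.
- The simulation error on 0.22 is √(0.22 × 0.78 / 40,000) ≈ 0.002.

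Losing patients is not what inflates the error rate: with ρ = 0 it stays at about 0.05 for every k. The link between withdrawal and outcome does, and the results-related ground is what permits that link.

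**The case against.** The strongest reply is that the clause permits withdrawal and does not require it, that reasons must be documented, and that this is a pilot. A transitory disease may have nothing to do with the drug, and setting it aside can be seen as protecting the EPO comparison from noise. The exclusion criteria already remove many patients likely to become ill: decompensated heart failure, expected dialysis, active malignancy, chronic infection and short life expectancy. No figure in the protocol shows that even one patient would leave on this ground.

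Much of this stands, and it limits what can be said. A reader might infer any of the following, and the document supports none of them:

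- **That the rule removes precisely the patients whose outcomes count against the drug.** It is discretionary, and some illnesses would be unrelated to treatment or outcome.
- **That adverse reactions vanish from the safety count.** The recording provisions set out in the check mean the triggering event should be captured. Only later events are at risk.
- **That the period before the infusion keeps its illnesses while the period after loses them.** A patient dropped from a paired comparison loses both periods. The protocol does not say which comparison would be made.
- **That withdrawn patients are excluded from the analysis.** The protocol does not say so. Analysis sets are commonly left to the statistical analysis plan, which was not available, so silence on this is no fault.

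What the reply does not meet is the stated rule itself. A possible effect on the results is given as a reason to take a patient out, and no follow-up is provided afterwards. If illness-related noise is a worry, it can be examined in the analysis with the patient still under observation.

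**Conclusion.** The point holds as a defect in a stated rule. The protocol allows an unblinded investigator to end a patient's participation because an event could affect the results, and the later EPO, hospitalisation, transfusion and renal data may then be lost. The direction is probably towards apparent benefit, because illness more plausibly raises than lowers these outcomes, but this is a judgement and the document does not establish it.

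The size cannot be determined. With a true effect of zero and 3 of 30 patients (10%) withdrawn, the false-positive probability lies between about 0.05 and 0.22, with 0.08 at moderate dependence. That range rests on normal changes, a paired two-sided test, an assumed number withdrawn and complete omission of those patients. If data up to withdrawal were kept and used, the bias would be expected to be smaller. The upper end is a bound for that scenario and not a forecast.

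**What to change.** In Patient withdrawal:

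1. Delete a possible effect on the study's results as a ground for withdrawal, and correct the garbled wording about the timing of the event.
2. Distinguish giving no further study medicine from leaving the study. This changes no clinical rule: the contraindication ground and the patient's own choice remain.
3. State that every dosed patient is followed to month 6 unless consent is withdrawn.
4. State, here or in the statistical analysis plan, that all dosed patients stay in the before-and-after and safety outcomes.

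Rates per patient-month, or a secondary analysis leaving out months of illness, are optional.

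The cost is protocol wording, continued attendance at visits already scheduled for the few patients affected, and possibly a slightly larger variance. In the scenario above, keeping all 30 patients brings the bias back to zero and the false-positive probability to about 0.05.
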